### Management of hepatitis C

Participants with hepatitis C infection (positive hepatitis C antibodies) will not be unblinded. However, they will be carefully monitored with liver function tests performed at least weekly until discharge, and then every 3–6 months for the full duration of the study. Liver function tests will be performed more frequently if there is a clinical need.

### Use of concomitant medication

All other concomitant medications essential for participant management are permitted at enrolment, subject to the exclusion criteria of no contraindications to the use of dexamethasone in the judgement of the attending clinician. If use of a concomitant medication that cannot safely be used with dexamethasone becomes essential after randomisation, then the study drug should be stopped and the concomitant medication used without unblinding. Drugs which increase the risk of gastrointestinal bleeding, such as non-steroidal anti-inflammatory drugs (NSAIDS), should be used with caution. Any other oral or intravenously administered corticosteroids are not permitted, unless deemed essential, in which case the study drug should be stopped and replaced by the chosen corticosteroid. Normal standards of clinical care should be followed.

### Management of neurological complications occurring after the start of anti-tuberculosis treatment

Corticosteroid use is not routine for the treatment of hydrocephalus or stroke, however for neurological deterioration secondary to tuberculomas most physicians recommend using corticosteroids. In this situation open-label dexamethasone is recommended. High-dose intravenous dexamethasone (0.4mg/kg/24hrs) should be prescribed, and the study drug stopped (if the study drug course is still ongoing).

## Data collection

The trial assessment schedule for the main trial is outlined in
Table 3.

**Table 3. T3:** Trial assessment schedule.

	DAYS					MONTHS				
	screening	0	R andom- isation	3	7	W eekly until discharge	30	60	M onthly to anti- TB drug end	12
ALL PARTICIPANTS										
Eligibility assessment	(X)									
Participant information sheet and consent	X									
Informed consent		X								
LTA4H genotype (5mls blood)		X								
Clinical assessment	(X)	X	X	X	X	X	X	X	X	X
Disability assessment							X	X	X	X
Chest X-ray	(X)							X		
Lumbar puncture (with paired plasma glucose)	(X)						X	X		
HIV test	(X)									
EDTA blood for genetic tests Full blood count Storage for later DNA extraction	(X)	X X			(X)					
Sodium Urea/Creatinine ALT/ bilirubin Hepatitis C antibodies Hepatitis B surface antigen Fasting blood sugar/HbA1c C-peptide/Lipids Strongyloides serology Serum Storage	(X) (X) (X)	X X X X X X			(X)	(X) (X) (X)		X X	(X) (X)	
Stool for Ova, cysts and parasites (Strongyloides) microscopy		X					X			
SUBSET OF PARTICIPANTS RECRUITED TO IMAGING STUDY (HTD only)										
Brain MRI		X						X		X
SUBSET OF PARTICIPANTS RECRUITED TO HYPONATRAEMIA/ICP SUB-STUDY (HTD only)										
24-hour fluid balance	(X)	X		X	X	X				
Plasma sodium Plasma osmolality		X		X	X	X				
Urinary sodium Urinary osmolality		X		X	X	X				
Plasma cortisol		X								
Doppler Ultra-sound assessment of intravascular volume		X		X	X	X				
Ultra-sound measurement of optic nerve sheath diameter		X		X	X	X				
SUBSET OF PARTICIPANTS RECRUITED TO ADRENAL SUPPRESSION SUB-STUDY (HTD only)										
Synacthen test						X (day 21)		X		

### Clinical assessment

Clinical assessment will include conscious level by GCS, new or ongoing focal neurological deficit, clinical treatment response, all serious adverse events, all adverse events of any grade leading to modification of anti-tuberculosis treatment or its interruption/early discontinuation (and clinician-assessed likelihood of relationship of adverse event to dexamethasone), and adherence to drugs (study drug and anti-tuberculosis drugs). Assessment of disability by the modified Rankin scale will be performed at day 30 from randomisation, monthly until completion of anti-TB drugs, and at month 12.

### Inpatient assessment

GCS and new focal neurology will be recorded daily during the participant’s hospital admission. Participants will be visited by one of the research team at screening, baseline, randomisation (when LTA4H genotype returns), and at least every 3 days for the first 4 weeks of treatment (unless they are discharged or die before 4 weeks) and then at least every 7 days whilst they remain in hospital. Formal trial clinical assessments will occur on day 0, 3, 7, 10, 14, and weekly thereafter until discharge (+/- 1 day).

### Outpatient assessment

After discharge clinical assessments will occur monthly until 12 months. Some of these assessments can be made by phone. Formal outpatient review will occur monthly (+/- 7 days) for at least the first 2 months following hospital discharge. The patient should have formal outpatient review at least every 2 months until month 12 after randomisation. The endpoints of survival and neurological disability by 12 months (-0/+1 month) should be assessed by formal outpatient review whenever possible.

### Liver function

Alanine transaminase (ALT) and bilirubin will be measured to evaluate liver toxicity every 7 days until discharge and at each subsequent follow-up visit until anti-tuberculosis treatment stops.

### Additional blood tests

EDTA blood will be taken for HBsAg, HBcAb, hepatitis B viral load, and hepatitis C antibodies. Serum will be stored for later DNA extraction when consent has been given.

### Glycosylated haemoglobin (HbA1c) and fasting blood sugar

HbA1c and fasting blood sugar will be measured at baseline and at 60 days from randomisation. To enable more detailed phenotyping of diabetes we will also measure C-peptide and blood lipids at baseline and store serum for future diabetes related auto-antibody testing.

### Strongyloides

All enrolled participants will be tested for serological evidence of Strongyloides infection at baseline (past or latent infection), and with stool examination for evidence of active infection at baseline and at 21–30 days from randomisation, depending on discharge date. When infection is detected, treatment with ivermectin will be provided. Stool will be examined for Strongyloides larvae at the end of study drug to determine whether reactivation alters TBM treatment responses.

### Synacthen test 

We will compare adrenal responsiveness at 3 weeks after randomisation and at the end of study drug treatment (6 or 8 weeks depending upon disease severity) in 100 consecutive patients using the short Synacthen test. The patient’s background cortisol level is measured by drawing 2mls of blood at 0900hrs. 250mcg of Synacthen is then administered intravenously; 3ml samples of blood are taken at thirty minutes and sixty minutes to measure the cortisol level after this adrenal stimulation. The Synacthen test will be repeated at day 60 after randomisation.

### Lumbar puncture

Lumbar puncture should be performed, unless clinically contraindicated, as part of routine clinical care for the baseline assessment, and on days 30 and 60 after randomisation to assess treatment response. Opening pressure should be measured, at least 5mls of CSF should be taken for mycobacterial investigations alone, and assessments of cell count and differential, protein, glucose, and lactate should also be performed on 1–2 mls of additional CSF. Ziehl Neelsen stain, GeneXpert, and
*M. tuberculosis* culture will be performed on all CSF taken. As part of an ancillary study of the impact of dexamethasone on CSF inflammation and gross cerebral pathology we will measure concentrations of a variety of inflammatory mediators in the CSF (leucocytes, cytokines, chemokines, and eicosanoids, for example) at baseline and on days 30 and 60 after randomisation to determine how dexamethasone influences their expression.

### Hyponatraemia and raised intracranial pressure

The rapid diagnosis of intracranial hypertension is challenging and urgently required in TBM. In the subset of participants enrolled to HTD, Ho Chi Minh City, Vietnam, we will investigate the pathophysiology of TBM-associated hyponatraemia by serial assessments of fluid balance, paired plasma and urinary sodium and osmolality, and intravascular volume by Doppler ultrasound assessment of inferior vena cava collapsibility index
^12,
13^. We will also use portable ultrasound to measure the optic nerve sheath diameter, which has been shown to be a reliable and non-invasive measure of raised intracranial pressure
^14,
15^. These additional measurements will be assessed at days 0, 3, and 7, and weekly until discharge. Plasma cortisol will be measured at day 0.

### Imaging

Chest Xray will be performed at screening and on day 60 after randomisation. Brain imaging by MRI (or CT if the participant cannot tolerate an MRI) will be performed at baseline (+/- 7 days), 60 days (+/- 7 days), and at 12 months (-0/+1 month). We will investigate whether dexamethasone influences the incidence and outcome of hydrocephalus, infarcts and tuberculoma formation in these participants.

## Adverse events and safety reporting

### Adverse events

Specific procedures will be followed when notifying and reporting adverse events (AEs) or adverse reactions (ARs). The definitions of the EU Directive 2001/20/EC Article 2 based on the principles of ICH good clinical practice (GCP) apply to this trial protocol. All AEs and ARs will be assessed as to whether they are serious or not. If the event is serious and not only related to TBM, or is fatal, then a serious adverse event (SAE) form must be completed and the OUCRU CTU notified within 24 hours. All AEs and ARs (serious and non-serious) should be graded using toxicity gradings.

Causality of all SAEs or serious adverse reactions (SARs) in relation to the trial therapy (dexamethasone) will be assessed. There are five categories: unrelated, unlikely, possible, probable, and definitely, related. If the causality assessment is unrelated or unlikely to be related, the event is classified as an SAE. If the causality is assessed as possible, probable or definitely related, then the event is classified as an SAR. If there is at least a possible involvement of the trial treatment (or comparator), the investigator must assess the expectedness of the event. An unexpected adverse reaction is one not previously reported in the current Summary of Product Characteristics (SPC) at the time the event occurred, or one that is more frequent or more severe than previously reported. If a SAR is assessed as being unexpected, it becomes a suspected unexpected serious adverse reaction (SUSAR). Investigators should always check the current version of the SPC.

### Safety reporting

The OUCRU CTU is responsible for the reporting of SUSARs and other SARs to the regulatory authorities and the research ethics committees. The following events will be reported to the relevant authorities in Vietnam: All unexpected SAEs, all SAEs judged to be related or possibly related to the trial intervention, and all deaths. All SAEs will be reported to OxTREC (Oxford Tropical Research Ethics Committee) in the annual review form and to the DMC in accordance to the DMC charter. An independent DMC will oversee the safety of the trial.

### Interim analyses

Interim analyses are planned 6-monthly during the first two years of recruitment and yearly thereafter until the completion of the trial but the DMC has the authority to modify the frequency of interim analyses. At these interim analyses, the DMC will receive a report including unblinded summaries of baseline characteristics, the primary endpoint, overall survival, and adverse events by treatment arm as well as conditional power curves for the primary endpoint. Statistical summaries will be provided both for all randomised subjects and for the subgroup of participants with CC and CT-genotype. The DMC may recommend termination or modification of the study in the circumstances that dexamethasone is harmful (placebo superior), or that dexamethasone is beneficial. The Haybittle-Peto boundary, requiring p < 0.001 at interim analysis to consider stopping for efficacy, should be used as guidance in both directions. This boundary may apply to the overall population with CC or CT genotype combined or either genotype alone. Importantly, a DMC recommendation will not be based purely on statistical tables, but will also require clinical judgment. The DMC will also review data from those enrolled into the drug-induced liver injury sub-study, in particular the incidence of acute hepatic failure in each of the management strategy arms.

## Statistical analysis

### Sample size justification – main trial

In a previous TBM trial
^4^, 73/189 (38.6%) of HIV-negative subjects with CC-genotype and 69/214 (32.2%) with CT-genotype experienced a neurological event or died during the 9 month follow-up period. Only few additional events are expected between months 9 and 12 of follow-up. All subjects in this trial received dexamethasone. In principle, administration of dexamethasone in CC and CT- genotypes would be discouraged if placebo could be shown to be non-inferior to dexamethasone. However, as the benefit of dexamethasone in the TT-genotype is undisputed and personalised administration of dexamethasone in HIV-uninfected subjects would necessitate rapid genotype testing, some evidence of harm of dexamethasone in the CC/CT population (or the CC group alone) is required. Therefore we have opted for a hybrid trial-design approach which assumes a modest harm of dexamethasone and aims to prove non-inferiority of placebo first but also allows claiming superiority of placebo in case dexamethasone proves to induce substantial harm
^16^. Moreover, as it is possible that harm of dexamethasone only applies to the CC-genotype, the trial should allow dropping the CT group at an interim analysis but continue randomisation of the CC group. To protect the one-sided overall familywise error rate of 2.5% for the analysis of the primary endpoint across the two co-primary populations (the full CC/CT population and the CC population), we will assign a multiplicity-corrected one-sided significance level of 2% to the full population and 0.87% to the CC population exploiting the correlation between test statistics on the two populations using the Spiessens and Debois method
^17^.

We set the non-inferiority margin in favour of dexamethasone at a hazard ratio (HR) of 0.75 and assume a true HR of 1.15 in the CC/CT population. Assuming an absolute risk of a neurological event or death in the dexamethasone group by 12 months of 35%, a HR=1.15 corresponds to risk of 31.2% on placebo, and the non-inferiority margin implies that we can exclude an absolute risk increase of placebo of (at worst) +8.7%. Under these assumptions a total of 184 neurological events or deaths would be required to obtain 80% power at the one-sided 2% significance level. Assuming an overall event risk of ≥32%, and an 11% sample size increase to compensate for loss-to-follow-up and reductions in power due to the allowance for stopping due to futility, a total of 640 HIV-negative subjects with CC or CT-genotype will be randomised into the trial. Based on experience from our earlier TBM trials
^4,
7,
18,
19^, only a very low number of subjects will be excluded from the per-protocol population, hence only minimally reducing power in this population. Of note, with 184 neurological events or deaths (half of them in the CC group), the trial also has 80% power to prove harm of dexamethasone in the CC/CT group or the CC group in case the true HR is at least 1.54 in all subjects or 1.96 in CC patients, respectively. Our recent trial enrolled 468 HIV-uninfected adults with TBM in 30 months and 90% of them had CC or CT-genotype. Assuming similar recruitment rates, enrolment will be complete within 4 years.

### Sample size justification – DILI strategy study

A review of 36 subjects who interrupted rifampicin and isoniazid because of clinical hepatitis or jaundice events from our previous trial
^4^ gave the following data: the median (interquartile range (IQR)) onset date of the drug-related liver injury was 50 (15–84) days from initiation of anti-tuberculosis treatment, the median (IQR) duration of the rifampicin and isoniazid interruption was 16 (12–24) days, and 12 subjects subsequently died (8 of them within 60 days). Of note, the duration of the treatment interruption was <t;30 days for 32 (89%) of the 36 subjects and the remaining 4 subjects never re-started rifampicin or isoniazid but continued to receive alternative anti-tuberculosis treatment for >100 days.

We hypothesise that strategies 1 and 2, respectively, will result in a relative reduction in the duration of the treatment interruption of 50% for subjects with interruptions <30 days, but that they do not affect longer interruptions (as the corresponding subject might have permanent intolerance to rifampicin and isoniazid) or mortality. Based on simulations of hypothetical trials using re-sampling from the data described above, the hypothesised treatment effect, and the Wilcoxon rank sum test for analysis, we determined that the power to detect such an effect size with a sample size of at least 50 subjects per arm is >85%. Of note, given this is an ancillary and essentially ‘opportunistic’ study, we have chosen a liberal (i.e. not multiplicity corrected) two-sided significance level of 5% for each of the two primary comparisons of strategies 1 and 2, respectively, versus strategy 3.

### Analysis populations – main trial

As the effect of dexamethasone may depend on the genotype with worse anticipated outcomes for CC-genotype, this trial has two co-primary analysis populations: The full analysis population containing all randomised patients and the subgroup of subjects with CC-genotype. Analyses in the subgroup with CT-genotype will also be performed but are exploratory only. In addition, the primary end point will be analysed in the per-protocol population, which will exclude the following patients: patients with a final diagnosis other than TBM, major protocol violations and those receiving less than 1 week of administration of the randomised study drug for reasons other than death. In all populations, patients will be analysed according to their randomised arm. For the analysis of the primary endpoint, a multiplicity corrected one-sided significance level of 2% for the full population and 0.87% for the CC subgroup will be applied as described in the sample size justification above. For all other analyses, the conventional two-sided significance level of 5% will be applied. Published diagnostic criteria
^20^ will be applied to all enrolled participants at the end of the study when all mycobacterial culture results are available (
Supplementary File 3). The criteria will sub-divide all cases into definite, probable and possible TBM, and those with an alternative diagnosis.

For the primary analyses of the main trial the second randomisation in the DILI strategy study will be ignored and the estimated dexamethasone treatment effect can thus be interpreted as an average effect across the three management strategies. We believe that this is justified because only approximately 70 (11%) subjects are expected to be enrolled in the nested trial with roughly similar numbers from both arms, because the efficacy of the different management strategies is unlikely to depend on whether the patient received dexamethasone or not as it tests a very different intervention, and because the anticipated effect of the management strategy on neurological events and deaths is relatively small. However, in a supplementary analysis, we will also compare the primary endpoint between the treatment policies “dexamethasone treatment plus standard of care management of drug-related liver injury” vs. “placebo treatment plus standard of care management of drug-related liver injury” using an inverse probability weighting based analytical framework
^21^.

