### Primary endpoint analysis – main trial

The primary endpoint of this trial is the time to death or a new neurological event during 12 months of follow-up. The primary endpoint will be analysed using a Cox proportional hazards regression model with treatment as the only covariate and stratification by TBM MRC severity grade at enrolment (I, II, or III) and LTA4H genotype (CC or CT). The primary effect measure is the resulting hazard ratio comparing dexamethasone vs. placebo with a corresponding confidence interval and p-value. Non-inferiority of placebo in the entire population or the CC-genotype subgroup will be established if the corresponding test (at the one-sided 2% or 0.87% significance level for the full population and the CC subgroup, respectively) rejects the null hypothesis that dexamethasone decreases the hazard of the primary endpoint by 25% or more. Superiority of placebo will additionally be established, if the null hypothesis that dexamethasone does not affect the hazard of the primary endpoint can be rejected against the one-sided alternative that dexamethasone causes harm. The distribution of the primary endpoint will also be visualized using Kaplan-Meier plots and explicit survival estimates at 3, 6, 9, and 12 months of follow-up will also be calculated.

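### The fixed levels of 2% and 0.87% control error correctly, but as a single-step rule they give up some power for the second population's claim that a closed test would recover at the same 2.5%

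*Protocol article*

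**What the plan says.** The Sample size justification for the main trial sets the aim: "To protect the one-sided overall familywise error rate of 2.5% for the analysis of the primary endpoint across the two co-primary populations". The levels come from the correlation-based method: "exploiting the correlation between test statistics on the two populations using the Spiessens and Debois method". The result is one-sided 2% for the full CC/CT population and 0.87% for CC.

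The same pair appears in Analysis populations, where "a multiplicity corrected one-sided significance level of 2% for the full population and 0.87% for the CC subgroup will be applied", and in the decision rule under Primary endpoint analysis: "at the one-sided 2% or 0.87% significance level for the full population and the CC subgroup, respectively". None of the three places makes one level conditional on the other test.

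The only sequential element lies within a population, from non-inferiority (margin HR 0.75) to superiority: "Superiority of placebo will additionally be established, if the null hypothesis that dexamethasone does not affect the hazard of the primary endpoint can be rejected". That sentence repeats no level. The power statement for harm is "80% power to prove harm of dexamethasone in the CC/CT group or the CC group in case the true HR is at least 1.54". This hazard ratio belongs to the full population; the one given for CC is 1.96. Both reproduce at 2% and 0.87%, so the same levels are evidently meant.

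**The concern.** The pair (2%, 0.87%) is needed while the null hypotheses of both populations are still open. By the closure principle, once one population's nulls have all been rejected, the other can be tested at the full 2.5%. The written rule keeps 0.87% (or 2%) in every case. When one population's null is false, the error actually spent on the other is therefore 0.87% or 2%, not the 2.5% that the plan allows itself.

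This bears on a claim that the trial cares about. The sample size section says that some evidence of harm in CC/CT, or in CC alone, is needed to justify genotype testing. The confirmatory CC claim rests on about 92 events at a strict level.

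**Working it through.** **Inputs from the protocol.** Allocation 1:1; 184 events, half of them in CC (92); margin HR 0.75; planning HR 1.15; harm HRs 1.54 (all) and 1.96 (CC); one-sided levels 2% and 0.87%; familywise error 2.5%. HR is dexamethasone versus placebo, so HR above 1 means harm. **Assumptions of this check:** the CT hazard ratios paired with CC 1.96; a single final analysis; SE of log HR = 2/√events.

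**Step 1: the plan's own figures.** Critical values are 2.054 (2%), 2.378 (0.87%) and 1.960 (2.5%).
- Events for non-inferiority: 4 × (2.054 + 0.842)² / [ln(1.15/0.75)]² = 183.5, so 184. Agrees.
- Harm in all: the mean of Z is √184/2 × ln 1.54 = 2.93; power = Φ(2.93 − 2.054) = 80.9%. Agrees.
- Harm in CC: the mean of Z is √92/2 × ln 1.96 = 3.23; power = Φ(3.23 − 2.378) = 80.2%. Agrees.
- Error under the global null: the correlation is √(92/184) = 0.707, and P(both reject) = 0.369%. So 2% + 0.87% − 0.369% = 2.50%. Agrees.

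**Step 2: the closed rule.** The intersection null is rejected if p_full ≤ 2% or p_CC ≤ 0.87%. Each population is then tested at 2.5%. For superiority:
- CC is rejected if p_CC ≤ 0.87%, or if p_full ≤ 2% and p_CC ≤ 2.5%.
- The full population is rejected if p_full ≤ 2%, or if p_CC ≤ 0.87% and p_full ≤ 2.5%.

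**Step 3: power for superiority of placebo.** Bivariate normal; the full-population log HR is the mean of the CC and CT log HRs.

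| HR in CC / CT | CC, written | CC, closed | Full, written | Full, closed | At least one claim, either rule |
|---|---|---|---|---|---|
| 1.96 / 0.8 | 80.2% | 80.6% | 29.9% | 33.0% | 80.7% |
| 1.96 / 1.0 | 80.2% | 82.5% | 59.0% | 62.0% | 83.4% |
| 1.96 / 1.15 | 80.2% | 84.8% | 75.9% | 77.8% | 87.3% |
| 1.54 / 1.54 | 37.9% | 52.9% | 80.9% | 81.1% | 81.7% |
| 1.15 / 1.15 | 4.4% | 6.9% | 13.4% | 13.6% | 14.8% |

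The CC hazard ratio detectable with 80% power falls from 1.96 to 1.92 (no effect in CT) or 1.80 (same effect in CT).

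**Step 4: error control.** Non-inferiority and superiority were simulated in both populations, with 4 million trials per configuration (Monte Carlo error about 0.008 points). The other population opens at 2.5% only after both claims are shown in the first.

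| True HR in CC / CT | Written rule | Closed rule |
|---|---|---|
| 1 / 1 | 2.50% | 2.50% |
| 0.75 / 1.33 | 2.50% | 2.50% |
| 1 / 3 | 0.87% | 2.51% |
| 2 / 0.5 | 2.00% | 2.50% |

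If alpha were released after non-inferiority alone, the configuration 0.75 / 1.33 would give 3.7%.

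**The case against.** The strongest reply is that nothing in the document is wrong. The levels agree wherever they are stated, the split is correct and the power figures hold. A single-step test is a legitimate choice, and the unseen analysis plan might add a step. All of this stands, except that such a step would change a rule that the article states three times without condition.

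The size of the gain is also easily overread. A reader might infer that the trial is more likely to miss harm altogether. It is not: the second step opens only after superiority is shown somewhere, so the probability of at least one harm claim is identical under both rules. A reader might also attach the 15-point gain (37.9% to 52.9%) to the case of harm confined to CC. That gain needs equal harm in both genotypes, and every added CC claim then comes in a trial that has already shown harm in the full population. In the CC-only case the gain is about 2 points, or 0.4 points if CT has HR 0.8. Non-inferiority hardly moves at the planning HR of 1.15: 37.1% to 38.4% in CC, and 80.1% unchanged in the full population.

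Two further points stand. The simulation has one look, whereas the protocol has repeated interim analyses and allows CT to be dropped while CC continues. And under a stepwise rule the confidence level that matches a decision in one population depends on the other population's result.

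**Conclusion.** The written rule is valid and should not be called an error. It is less efficient than a closed test with the same first step, which makes every rejection that the written rule makes and adds others at the same 2.5%. The gain lies only in the second population's claim: 2 to 5 points of power for CC superiority at CC HR 1.96 with CT HR 1.0 to 1.15, 15 points at HR 1.54 in both, and under 3 points at the planning HR of 1.15. These figures assume 184 events, a 50% CC share, the CT effects shown and a single final analysis. Error control after CT is dropped at an interim has not been checked. The point is minor, but worth taking before unblinding because it costs almost nothing.

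**What to change.** Keep 2% and 0.87% as the first step and add:
- If non-inferiority and then superiority are both shown in the full population at 2%, test CC (non-inferiority, then superiority) at one-sided 2.5%.
- If both are shown in CC at 0.87%, test the full population in the same order at one-sided 2.5%.
- Release no alpha after non-inferiority alone.
- Apply the step only at the final analysis, with both genotypes randomised to completion. Otherwise the fixed levels stand, unless error control with CT dropped has been shown.
- Report confidence intervals at the fixed first-step levels, and say that a second-step decision may not match its interval.

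The cost is a few sentences, written before unblinding, and that mismatch between interval and decision. No patients or data are needed.

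Recomputing 0.87% from the realised CC share of events is optional. The earlier trial's counts in the sample size section, 73 of 142 events in CC (51%), give a familywise error of 2.49%. Assumed shares of 45% and 40% would give 2.54% and 2.58%.
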